### Data analysis

The primary outcome is the post-treatment score on the HRSD, which is treated as a continuous, normally distributed variable. The primary efficacy hypothesis will be tested by using a multilevel two-group comparison (g-RFCBT versus g-CBT), with group as a main effect, therapy group as a random intercept, and the HRSD baseline score as a continuous covariate [41]. The test will be performed at the 5 % two-tailed significance level [42].

The primary test for efficacy will be based on the intention-to-treat population with all randomised patients entering the analysis set. The multiple imputation method will be used for missing data when appropiate [42].

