### Eligibility criteria

Patients who are between 18 and 65 years of age and who meet Diagnostic and Statistical Manual of Mental Disorders, 4th Edition (DSM-IV) criteria for a current episode of unipolar major depression or recurrent or chronic depression in a structured M.I.N.I. 5.0 interview and with a score of 13 or more on the 17-item HRSD can be included [18]. Patients with psychotic symptoms, bipolar disorder, functional illiteracy, or alcohol and drug abuse will be excluded. Patients with depression and co-morbid anxiety or personality disorder are included in the study. Patients receiving anti-depressants will not be excluded.

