### Randomisation and concealment

Participants will be allocated in a 1:1 ratio to either g-CBT or g-RFCBT. The randomisation will be concealed from the investigator by use of an off-site computer-based randomisation. Patients are randomly assigned in blocks of variable sizes (6–10) according to a pre-study computer-generated (Microsoft Excel 2011; Microsoft Corporation, Redmond, WA, USA) randomisation list to receive one of the two treatment options.

All assessments will be conducted equally in both treatment conditions by researchers blind to randomisation. To successfully maintain the blinding throughout the trial, the researchers conducting the patient assessments will be instructed to remind the patients of the confidential nature of their treatment.

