In addition, all participants will be offered clinical management and treatment with anti-depressant medication if needed, as evaluated by a highly trained and experienced psychiatrist at the outpatient service. There are no restrictions in use of anti-depressant medication in this trial, but use of anti-depressive medication and changes in type of medication or dosage will be registered.

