### Adverse events

All adverse events will be monitored by the psychotherapists and the psychiatrists at the outpatient service and reported in the patient case report. If a patient is at risk of an adverse event, a psychotherapist, psychiatrist, or research staff will take immediate action to prevent any adverse event from happening. Use of anti-depressive medication will be administered and monitored by experienced psychiatrists at the outpatient service. There are no study-specific restrictions on change of dosage of or types of anti-depressant medications. Medications, adverse effects due to medication, and changes in medical treatment will be reported in the patient case record by the psychiatrists. We will compare the levels of usage of anti-depressant medication and the reported adverse effects across the arms by conducting a screening of the participants’ case reports when all participants have finished treatment.

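### The primary model leaves out baseline antidepressant use; the test is valid, but prespecifying this covariate would add a little precision and protect against chance imbalance

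*Protocol article*

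**What the plan says.** All the relevant statements are in the protocol article.

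- **Eligibility criteria:** "Patients receiving anti-depressants will not be excluded". No period of stable medication before entry is stated.
- **Interventions:** antidepressants may be given freely during the trial, without any study limit. On what is recorded, the article says: "use of anti-depressive medication and changes in type of medication or dosage will be registered".
- **Randomisation and concealment:** "Participants will be allocated in a 1:1 ratio to either g-CBT or g-RFCBT", and "Patients are randomly assigned in blocks of variable sizes (6–10) according to a pre-study computer-generated" list. No stratification factor is named.
- **Data analysis:** the primary model compares the arms with "therapy group as a random intercept, and the HRSD baseline score as a continuous covariate", by intention to treat, at a two-sided 5 % level. It has no medication term.
- **Adverse events:** "We will compare the levels of usage of anti-depressant medication and the reported adverse effects across the arms", by screening case reports once everyone has finished treatment.

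**The concern.** Antidepressants act on the construct that the primary endpoint measures. Two patients with the same baseline HRSD, one unmedicated and one with symptoms persisting on medication, may have different expected courses whichever therapy they receive. Baseline HRSD need not capture that difference in full.

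The stated design uses this information neither in allocation nor in the primary estimate. The planned comparison of usage between arms would describe an imbalance but leave the estimate as it is. A covariate added after that comparison had been seen would be post hoc.

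Two things are at stake, both modest. Variation that a baseline covariate could explain stays in the residual error, and a chance imbalance in this particular trial stays in the estimated contrast. If an imbalance did occur, the result would also be harder to defend without a prespecified adjustment.

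**Working it through.** **Step 1: reproduce the plan's own figures (Sample size estimation).** The planned difference is 7.81 − 3.52 = 4.29 points. With SD 6 this is 4.29/6 = 0.715, which the plan takes as 0.7. A two-sample t-test at two-sided 5 % and 90 % power needs 43.87, so 44 per arm. Allowing for 20 % dropout, 44/0.8 = 55. Both figures agree with the plan.

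**Step 2: power at the planned size.** With 64 recruited per arm and 20 % dropout, 64 × 0.8 = 51.2 remain. The plan's design effect is 1 + 7 × 0.05 = 1.35, so the effective number is 51.2/1.35 = 37.9 per arm. By the normal approximation, power is Φ(0.7 × √(37.9/2) − 1.96) = Φ(1.09) ≈ 86.2 %. This is below 90 % because 128 patients do not cover dropout and clustering together (55 × 1.35 = 74.25 per arm). That is a separate matter; 86.2 % serves here only as the reference value.

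**Step 3: assumptions.** The documents give neither the share of users at baseline (p) nor the effect of use on post-treatment HRSD (b). I take p = 0.3 to 0.7, b = 1 to 3 points, and the plan's SD of 6.

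**Step 4: chance imbalance.** With 64 per arm, the SD of the difference in proportions is √(2p(1 − p)/64). The shift in the contrast at an imbalance of 1.96 SD is b × 1.96 × SD.

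| p | SD of difference | P(gap ≥ 10 points) | shift, b = 1 | b = 2 | b = 3 |
|---|---|---|---|---|---|
| 0.3 or 0.7 | 0.081 | 0.22 | 0.16 | 0.32 | 0.48 |
| 0.5 | 0.088 | 0.26 | 0.17 | 0.35 | 0.52 |

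For scale, the standard error of the contrast without clustering is 6 × √(2/64) = 1.06 points.

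**Step 5: precision.** The variance explained is R² = b²p(1 − p)/36. Adjusted power is Step 2 with the residual SD multiplied by √(1 − R²).

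| b | R² (p = 0.3 or 0.7; p = 0.5) | adjusted power |
|---|---|---|
| 1 | 0.006; 0.007 | 86.4 %; 86.4 % |
| 2 | 0.023; 0.028 | 87.0 %; 87.1 % |
| 3 | 0.053; 0.063 | 87.9 %; 88.3 % |

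The gain is about 0.2 to 2 percentage points. Two simplifications apply: the design effect is held at 1.35 after adjustment, and nothing is deducted for what baseline HRSD already explains. That deduction would make the gain smaller.

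**Step 6: validity of the unadjusted test.** In 20,000 simulated trials with no therapy effect (64 per arm, half users, b = 2, SD 6, no clustering), the unadjusted t-test rejected in 4.96 % and the mean estimate was −0.005. Leaving out the covariate neither inflates the error rate nor biases the estimate over randomisations.

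**The case against.** The strongest reply is that nothing here is wrong. A randomised comparison adjusted for baseline HRSD, with therapy group as a random intercept, is a sound primary analysis. Chance imbalance is what the standard error and the 5 % level already allow for. This stands in full. A reader might infer from the free use of medication that the primary estimate is biased or the test too liberal. The documents do not support that, and Step 6 shows the opposite.

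The size rests on assumed inputs. This also stands. The shifts in Step 4 need an imbalance at the edge of the 95 % range, and the largest is about half of one standard error (0.52/1.06).

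Other baseline features in the article, such as chronicity, recurrence and co-morbidity, could predict outcome equally well. That is fair. Antidepressant use is chosen because it acts directly on the endpoint and is already registered, not because the documents single it out.

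A reader might also want to adjust for medication over the whole trial, since prescribing is unrestricted. The documents do not support that either. Changes after randomisation may be affected by the therapy, and they belong to the pragmatic intention-to-treat contrast. Adjusting for them could introduce bias.

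Nor can it be assumed that recently started or changed medication can be separated from long-standing use. The article promises registration of use and of changes in type or dosage, but does not say that dates before baseline are captured.

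Finally, further covariates may sit in an analysis plan that is not shown. If so, the point falls away. As published, however, the Data analysis section lists the terms of the primary model, and the comment concerns that list.

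**Conclusion.** The point holds as a small, optional improvement. Baseline antidepressant use is absent from both the described randomisation and the stated primary model, and the end-of-trial comparison of usage does not adjust the estimate. The loss is one of precision and of protection against imbalance in this single trial. Validity is not affected.

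Under the Step 3 assumptions, an unusually large imbalance would move the contrast by at most about 0.5 points (0.52/4.29, or 12 % of the planned difference), and adjustment would add at most about 2 percentage points of power. Both figures depend on inputs that the documents do not supply, and the power gain shrinks to the extent that baseline HRSD already carries the information.

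**What to change.** In the Data analysis section, add antidepressant use at baseline (yes/no) as a fixed covariate beside baseline HRSD. Fix this before unblinding and record it as a dated change to the published model. Take the status only from information that precedes randomisation. Use a finer category for a recent start or change only if those dates are already recorded for all patients, with the time window set in advance. State that medication started or changed after randomisation will not be adjusted for.

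The cost is one sentence and one degree of freedom. The sponsor should first confirm that baseline use is on record for every patient, since the article says use is registered but not at what time point. Eligibility, prescribing, visits and the intention-to-treat question are unchanged. Allocation is already under way, so the fix leaves the randomisation alone.

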### Ethical considerations

We will conduct the trial in such a way as to protect the human rights and dignity of participants as reflected in the Helsinki Declaration [43]. The patients will be informed about the research project and purpose of the project prior to participation and asked for informed consent. No side effects due to the RFCBT have been reported. It is not possible to pay the patients for participating in the research project. We will follow good clinical practice in monitoring for suicide risk during all research and clinical encounters with trial participants. If any risk to participants due to expressed thoughts of suicide is encountered, we will report these directly to the psychiatrist responsible for treatment of the patient (with the participant’s expressed permission), and if an acute risk is present, we will arrange for an immediate assessment by the psychiatrist responsible for the treatment or follow the patient to the psychiatric emergency room for further assessment of need of hospitalization. The project has been approved by the Danish National Ethical Scientific Committee (registration number H-1-2013-049) and is registered at the Danish Data Protection Agency by the Mental Health Services of the Capital Region of Denmark.

## Discussion

Previous research supports rumination as a common residual symptom of depression that remains elevated after both partial and full remission. Elevated rumination is associated with diminished responsiveness to anti-depressant medication and cognitive therapy [44, 45], and rumination has been demonstrated as a crucial factor in vulnerability to depression, predicting the onset, severity, and duration of future depression [16]. The preliminary research on the effectiveness of RFCBT shows promising results compared with TAU [18]; furthermore, targeting rumination may improve relapse rates. In addition, no trial has directly compared g-RFCBT with g-CBT, and this randomised study may provide the first support for g-RFCBT as a potential alternative to g-CBT treatment. This may be relevant for patients who have not responded to CBT or for other reasons prefer a different, but still evidence-based, treatment for depression. The group format of delivering therapy is more cost-effective than individual therapy, which is widely used in CBT treatment for depression in outpatient services in Denmark. Service managers as well as the patients would most likely welcome a cost-effective treatment for depression with good outcome and reduced relapse rates.

This trial is conducted in a naturalistic setting on a heterogeneous sample of patients with recurrent depression, a single episode of depression, or chronic depression, and co-morbidity with anxiety and occasionally with personality disorder. The results are highly generalisable to the actual clinical reality in many outpatient services in Denmark. The treatment that is being tested in the present trial is robust as to heterogeneity and co-morbidity and even has potential as a transdiagnostic treatment for emotional disorders.

## Trial status

Recruitment commenced in October 2013 and is ongoing.

## Abbreviations

BADS: Behavioural Activation for Depression Scale
CBT: Cognitive Behavioural Therapy
CTRS: Cognitive Therapy Rating Scale
DSM-IV: Diagnostic and Statistical Manual of Mental Disorders, 4th Edition
GAD-7: Generalised Anxiety Scale
g-CBT: Group-based standard cognitive behavioural therapy
g-RFCBT: Group-based rumination-focused cognitive behaviour therapy
HAM-D6: 6-item Hamilton Depression Rating Scale
HRSD: Hamilton Rating Scale for Depression
PSWQ: The Penn State Worry Questionnaire
RFCBT: Rumination-focused Cognitive Behavioural Therapy
RRS: Rumination Response Scale
TAU: Treatment-as-usual
